## Missed Visits

In case of a no-show at the clinic for a scheduled study visit, study personnel will call the caregiver and visit the child’s home either that afternoon or the following day to conduct the study visit. Maximum efforts will be made to ensure complete follow-up in the trial. For children who do not complete a scheduled visit within the visit window, that visit will be documented as “missed” but study staff will still attempt to complete the appropriate assessments from that visit, if possible (e.g., Day 6 visit performed and documented on Day 9).

Children who miss a visit, for other than a protocol-mandated reason for discontinuation, are permitted to continue with any subsequent study treatments that can still be scheduled in the time interval specified by the protocol.

Based on our current experience, we expect that fewer than 5% of the children will be lost to follow-up at the time of primary outcome assessment. We think it is unlikely that attrition rates will differ between randomization groups.

## Interim Contacts and Visits

Interim contacts and visits (those between regularly scheduled follow up visits) may be performed at caregiver request or as deemed necessary by the site investigators or designee at any time during the study. All interim contacts and visits will be documented in the child’s study records and on applicable case report forms (CRF). Interim visits may occur at the study clinic or at the child’s home.

## Therapy for Treatment Failure and Clinical Relapse

If a child is determined to have treatment failure on or before Day 6 or clinical relapse between Day 6 and Day 14, he or she will be hospitalized and will receive second-line therapy. At KCH, standard of care for children failing oral amoxicillin is to receive benzyl penicillin and gentamycin. Enrolled children failing treatment or experiencing clinical relapse will receive this regimen as inpatients, regardless of their randomization allocation.

## Withdrawal and Early Termination

Children and their caregivers may voluntarily withdraw from the study for any reason at any time. The site investigators may also withdraw children from the study in order to protect their safety if, in the investigators’ opinion, continuing participation would jeopardize the child’s health. Any participant withdrawal or early termination will be documented in the appropriate study forms.

If a child withdraws from the study during the first 3 days of treatment, s/he will be referred to care with the recommendation that the child receive oral amoxicillin for a full 5-day treatment course. If a child withdraws from the study after completing the first 3 days of treatment, but before completing the full 5 days of study product, the child will be referred to care with the recommendation that s/he receive an additional 2 days of treatment with oral amoxicillin.

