  - Any time before or on day 6: WHO IMCI danger signs, severe respiratory distress (e.g., grunting, nasal flaring, head nodding, or severe chest-indrawing), oxygen saturation by pulse oximetry < 90%, missing 3 or more doses due to vomiting, change in antibiotics prescribed by a study clinician, or death.
  - At or after initial hospitalization discharge assessment (between 42 and 60 hours post-enrollment): documented axillary temperature > 38 ºC with chest-indrawing.
  - At day 6 outcome assessment: persistence of chest-indrawing, or axillary temperature > 38 ºC.
  - For the purposes of this protocol, children who do not fail on assessment at day 6 will be considered clinically cured. Loss to follow-up or withdrawal from the study at any time after enrollment and before the day 14 follow-up visit will be considered missing outcome data for that respective time point.
- *Clinical relapse* will be defined as recurrence of signs of chest-indrawing pneumonia, severe respiratory distress (e.g., grunting, nasal flaring, head nodding, or severe chest- indrawing) or severe disease after day 6 among those who did not have treatment failure at or by day 6.

Recruitment and follow-up is expected to continue until the maximum sample size is achieved. For the chest-indrawing pneumonia study a total of 2,000 children (1,000 per treatment group) will be enrolled. We are assuming a treatment failure rate of 8% in the 5-day control group and a relative 1.5 non-inferiority margin. Figure 3 shows the maximum true failure rate in the 3-day treatment group in reference to various possible failure rates in the 5-day treatment group and a 1.5 relative non-inferiority margin (50% relative increase in failure rate) that would result in a 95% confidence interval at maximum enrollment which excludes the non-inferiority margin. The figure also indicates the power the study has to show non-inferiority if the failure rates are exactly the same in the two treatment groups for various possible failure rates. Of note, the estimated power is adjusted for a 5% loss to follow-up rate in each of the arms. This is considered conservative with respect to the multiple imputation procedure that will be used to account for missing outcome values.

**Figure 3.** Chest-indrawing pneumonia failure rates

Note:

- Blue, solid circles, blue number below: Potential failure rates for the 5-day treatment group.

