To account for anticipated loss to follow-up or study withdrawal we will use multiple imputations for any missing outcome data. We will then perform sensitivity analyses to assess how the results might change with varying imputation assumptions. More information is provided in section 8 below.

1. **HANDLING OF MISSING DATA AND OTHER DATA CONVENTIONS**

We have estimated that loss to follow-up or study withdrawal will be 5%. Children lost to follow-up cannot be classified as improved or treatment failures at the missed visit. We will use multiple imputations for any missing outcome data. The imputations will be performed separately for each treatment group and cohort using multiple (20) hotdeck imputations and other information as described below. Multiple imputation estimates will be combined using Rubin’s approach[3].

Specifically, for each episode that is missing outcome data, we will create a subset of episodes that match exactly on treatment arm and gender while matching on age category, highest educational level achieved by the mother (none, primary, secondary, tertiary, while combining these categories for categories with less than 5% of participants, if needed, unknown education level will be multiply imputed, independent from outcome imputation) and adherence information (all combinations of categories for

a) days 1-3: no missing doses, 1-3 missing doses, 4-6 missing doses and

b) days 4-5: no missing doses, 1-2 missing doses, 3-4 missing doses,

unknown dosing information will be conservatively imputed as “not taken” for the 3 day arm and similar to patients where dosing is available for the 5-day arm). We will then randomly select one episode from the corresponding subset with complete information and use its values to replace the entire episode with missing outcome data.

We will repeat this process for each episode missing outcome data and calculate failure rates for both treatment arms using the imputed outcome. We will repeat this 20 times and determine the mean failure rates for each treatment arm. The difference between the mean failure rates will be calculated. Noninferiority bounds as listed in 7.2 will be consulted.

1. **SENSITIVITY ANALYSIS**

We will perform sensitivity analyses to assess how our results might change if the imputation assumptions are changed in a reasonable way, informing the robustness of the primary analysis result. We will perform complete case analysis as one form of sensitivity analysis.

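### Section 4.6 treats stopping study product and leaving the study as one event, so a child taken out unwell but short of a failure criterion has an imputed, not observed, Day 6 outcome

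*Combined protocol and SAP*

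**What the plan says.** **Withdrawal.** Protocol section 4.6 (Withdrawal and Early Termination) allows caregivers to take a child out for any reason. It adds: "The site investigators may also withdraw children from the study in order to protect their safety". The event is documented and the child is referred. A child leaving in the first 3 days is advised to take a full 5-day course of oral amoxicillin; one leaving later is advised to take 2 more days. No later outcome visit is described.

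**Missed visits.** Section 4.6 (Missed Visits) is different. After a missed window, "study staff will still attempt to complete the appropriate assessments from that visit", with a Day 6 visit done on Day 9 as its example.

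**Status of the outcome.** Under section 5.1 (Objectives and Endpoints), "withdrawal from the study at any time after enrollment and before the day 14 follow-up visit will be considered missing outcome data". The same section has criteria that apply only at the end of treatment: "At day 6 outcome assessment: persistence of chest-indrawing, or axillary temperature" above 38 °C.

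**Imputation.** In SAP section 8, for a missing outcome, "we will create a subset of episodes that match exactly on treatment arm and gender while matching on age category", mother's education and dose adherence on Days 1-3 and 4-5. Unknown doses are set to not taken "for the 3 day arm and similar to patients where dosing is available for the 5-day arm". The list in protocol section 5.1 (Final Analyses) differs slightly, but it too has no clinical sign and no reason for leaving.

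**Sensitivity.** SAP section 9: "We will perform sensitivity analyses to assess how our results might change if the imputation assumptions are changed in a reasonable way". Then: "We will perform complete case analysis as one form of sensitivity analysis". No other form is named.

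**The concern.** Leaving because a child is unwell or not improving is related to the outcome. If such a child would have met a failure criterion at Day 6, the trial does not see it and substitutes the result of a child who may have been doing well. The complete-case analysis removes the same child, so it cannot show whether this matters.

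The primary comparison can turn on few events. If enough true failures were hidden in the 3-day arm and not in the 5-day arm, non-inferiority could be claimed too easily. An opposite imbalance would make it harder to claim.

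**Working it through.** **1. Who is affected.** Protocol section 3 and SAP section 6.1 already count as failure, at any time up to Day 6: danger signs, severe respiratory distress, oxygen saturation below 90%, repeated vomiting of doses, an antibiotic change by a study clinician, and death. From the discharge assessment (42-60 hours), fever with chest-indrawing also counts. What remains is mainly isolated chest-indrawing or isolated fever before Day 6. Before the discharge assessment even the two together do not count, but both arms take the same active drug on Days 1-3. The referral in section 4.6 is for oral amoxicillin again, so it would not clearly count as an antibiotic change.

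**2. The plan's own figure.** Inputs from section 4.5: 950 evaluable per arm, 8% failure in both arms, 4-point margin, stated power 88%. SE = √(2 × 0.08 × 0.92 / 950) = 0.01245. Power = Φ(0.04/0.01245 − 1.96) = Φ(1.253) = 89.5%. Simulation with the limits in SAP Tables 1 and 2 gives 87.4%. The 88% is reproduced.

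**3. How many failures matter.** With 1,000 per arm and a fixed 4-point margin, the upper limit is a − b + 1.96 × √([a(1−a) + b(1−b)]/1000), where a and b are the 3-day and 5-day failure rates. At 80 v 80 failures it takes 16 more in the 3-day arm to lose non-inferiority; at 90 v 80 it takes 6. If 1% of the 3-day arm (10 children) left, all truly failing, and were imputed at 8%, the difference would be understated by 0.01 × (1 − 0.08) = 0.92 points, about 9 failures.

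**4. False-claim risk.** No document gives withdrawal counts by reason or donor failure rates, so all shares below are assumptions. True rates are set at the margin: p3 = 12%, p5 = 8%.

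- w = share of an arm withdrawn while truly failing with no criterion recorded; d = failure rate of its donors.
- Rate seen: o = (p − w) + w·d. If donors fail only as often as the children who stay, o = (p − w)/(1 − w).
- Risk = Φ(−1.96 − (o3 − 1.5·o5)/SE), with SE² = [o3(1 − o3) + 2.25·o5(1 − o5)]/950.

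This SE lets the margin move with the observed control rate, and gives exactly 2.5% when nothing is hidden. Imputation variance is ignored.

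Example, 1% v 0 with donors like stayers: o3 = 0.11/0.99 = 11.11%, o5 = 8%, SE = 0.01668, risk = Φ(−1.96 + 0.533) = 7.7%.

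| w, 3-day v 5-day | donors like stayers | d = 50% | d = 80% |
|---|---|---|---|
| 1% v 0 (about 10 v 0 children) | 7.7% | 4.8% | 3.3% |
| 0.5% v 0 (about 5 v 0) | 4.5% | 3.5% | 2.9% |
| 2% v 1% | 4.4% | 3.5% | 2.9% |
| 1.2% v 0.8% (proportional to failure) | 2.3% | 2.5% | 2.5% |
| 1% v 1% | 1.1% | 1.7% | 2.2% |
| 0 v 1% | 0.2% | 0.8% | 1.6% |

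With a shared fixed d, o3 − 1.5·o5 shifts by −(1 − d)(w3 − 1.5·w5). The bias therefore favours non-inferiority only if such withdrawals are more than 1.5 times as frequent in the 3-day arm (about 1.56 times with donors like stayers).

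**5. The unknown-dose rule.** If it applies, 3-day children are matched to donors with missed doses. These may include early failures moved to second-line therapy, which is an inference. Taking 3-day donors at 50% or 80% failure and 5-day donors like stayers, the risk is 1.4% or 0.5% at 2% v 1%, 1.1% or 0.6% at 1.2% v 0.8%, and 0.6% or 0.35% at 1% v 1%. At 1% v 0 it stays at 4.8% or 3.3%. At 2% v 1% it passes 2.5% only if 3-day donors fail at less than about 30%.

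**The case against.** The strongest reply is that hardly anyone is affected. A clinician worried about a child can change the antibiotic, and that is already failure, so the investigator route is close to empty. Lack of improvement is not named in section 4.6; it is read into the caregiver's freedom to leave. Dose adherence on Days 4-5 is a matching variable, so a recorded stop carries some clinical information. Staff and caregivers are blinded and Days 1-3 are identical, so an arm-related imbalance could arise only from Day 4. The SAP promises analyses under changed imputation assumptions, with complete case as one form among others. Interim visits are allowed when investigators see a need, and the study forms, which are not in the documents, may already hold a reason for withdrawal.

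Most of this stands and sets the size of the point. It does not supply a Day 6 assessment. The interim-visit and tracing provisions concern children still in the study, and the promised analyses name no assumption suited to these children.

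A reader might infer more: that investigators can remove failing children from the endpoint, or that the plan tilts the trial towards non-inferiority. The documents do not support either. The existing criteria catch most clinically evident failures, and the direction depends on an imbalance that no document indicates. The 7.7% figure needs about 10 v 0 hidden failures together with donors who fail only as often as stayers. Nor does the unknown-dose rule settle the matter the other way, as the 1% v 0 case shows.

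**Conclusion.** The gap is real and narrow. A child taken out before Day 6 with isolated chest-indrawing or isolated fever has no described outcome assessment, and is imputed without last clinical signs or reason for leaving. The plan expects 5% loss or withdrawal in total and does not say how much of it is of this kind; it is probably a small part. With equal or proportional withdrawals the false-claim risk is at or below 2.5%. It rises above that only under an assumed imbalance towards the 3-day arm of more than about 1.5 to 1, and then depends on how often the donors fail. These figures rest on true rates exactly at the margin, assumed shares and ignored imputation variance. The point is minor. It is worth acting on because observed outcomes can replace imputed ones at little cost.

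**What to change.** 1. In protocol section 4.6, separate *stop study product* from *withdraw from the study*. After a product stop, keep the Day 6 and Day 14 assessments, in clinic or by the existing home visit, unless the caregiver refuses follow-up. Record any antibiotic taken after the stop.
2. In SAP section 9, name one of the promised sensitivity analyses: count withdrawals on or before Day 6 for safety, deterioration or lack of response as failures in both arms. Leave the primary endpoint unchanged. This needs the reason for leaving, coded blind to arm, if the withdrawal form does not already hold it.
3. Report these children separately, by arm.

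The cost is wording in two places, possibly one form field, and a few extra visits by the home-visit team already planned. There are two downsides. Failure rates will be slightly higher in the sensitivity analysis. The amoxicillin advised after leaving may also make 3-day-arm outcomes resemble the control regimen and narrow the contrast, which is why item 3 is needed. Some caregivers will refuse follow-up, and their children will still be imputed.

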## Study Termination Visit

The Day 14 visit will serve as the study termination visit. Procedures for this visit, in addition to the standard follow-up visit procedures described above, include the following:

- - Collect any unused study product from caregiver, if not retrieved at prior study visit
  - Refer child to clinical care, as needed
  - Document contact in child’s study records

## Biohazard Containment

As exposure to blood-borne pathogens can occur through contact with contaminated needles, blood, and blood products, appropriate blood and secretion precautions will be employed by all personnel in the HIV, anemia, and malaria testing for this study as recommended by the U.S. Centers for Disease Control. Biohazardous waste will be contained according to institutional, transportation/carrier, and all other applicable regulations.

## STUDY PRODUCTS

## Presentation and Formulation

Prepared study product will be labeled by the manufacturer so as to maintain the blind; both the amoxicillin DT packages and the placebo DT packages will have the same printed information (e.g., “ITIP Study Product - dispersible tablets 250 mg”). This is a double-blinded study in which the study drug assignment will be concealed from the child, caregivers, and study personnel (with the exception of the study pharmacists and the Protocol statisticians). Labels will meet all national and local requirements. The label must also include the product expiry date, batch number, manufacture date.

For this study, amoxicillin DT is supplied as round, orange, uncoated tablets that contain 250 mg of amoxicillin and inactive ingredients. The placebo formulation for this study is a dispersible tablet that appears, tastes, smells, and disperses indistinguishably from the amoxicillin DT, although it is composed of only the inactive ingredients.

Study drug (amoxicillin DT and placebo DT) will be supplied in bulk shipments by a Sponsor-contracted drug manufacturer to the study site. Active drug and placebo pills will be sent in separate shipment packaging to avoid any mis-identification on the part of the study pharmacists, the only un-blinded study staff members in Malawi. The study pharmacists will prepare study product kits in batches based on the stratified randomization list. The amoxicillin DT and placebo DT will be individually labeled by the study pharmacist with each child’s participant ID number printed on self-adhesive sticking labels. Different ID sequences and/or label colors will be used for the three age bands to minimize the chances of a prescription error. The link between the participant ID numbers and randomization code will be kept securely by the study pharmacists.

Amoxicillin DT is commercially available in blister packs containing 10 tablets per blister pack. Each child’s study product supply will be re-packaged by the study pharmacists in kits based on the child’s age band and randomization allocation. Each kit will represent the entire study product supply for one child. A supply of 5 days-worth of study product will be dispensed based on the child’s age band. Each child’s kit will consist of a package of amoxicillin tablets labeled for the first 3 days and a separate package labeled for days 4 and 5 of treatment, either placebo or amoxicillin (refer to Table 1 below).

**Table 1.** Study Product Kits of Amoxicillin DT or Placebo DT, to be taken twice daily

| **Age Band** | **No. of tablets provided** | |
| --- | --- | --- |
| **Days 1-3*** | **Days 4-5** |
| 2 months up to 12 months | 6 | 4 |
| 12 months up to 3 years | 12 | 8 |
| 3 years up to 5 years | 18 | 12 |

*These tablets will all have active drug, regardless of randomization allocation. All other tablets will be either placebo or active drug, based on randomization arm.

## Preparation and Administration

The amoxicillin DT will be provided in 250 mg doses according to the age bands noted in Table 2 and will be administered orally to the child in divided doses twice daily by dispersing in a small amount of clean water or breast milk and provided.

**Table 2.** Study Product Administration by Age Band

| **Age Band** | **Oral Amoxicillin/Placebo Dispersible Tablets (DT)** | |
| --- | --- | --- |
| No. of 250 mg tablets, given two times daily | Total study product administered per day |
| 2 months up to 12 months | 1 | 500 mg |
| 12 months up to 3 years | 2 | 1,000 mg |
| 3 years up to 5 years | 3 | 1,500 mg |

Study drug will be maintained and dispensed to the participant caregiver by a study pharmacist. As noted above, the study pharmacists will package tablets received as bulk study drug. Tablets will be used as supplied, meaning that other than packaging and labeling, there is no further study drug preparation required. Study drug is administered orally in either clean water or breast milk, as appropriate. For breast milk administration, the mother will need to express at least 5-10 ml of breast milk into a clean container before dispersing the study product into the liquid. If a mother is unable or unwilling to express milk at the time of study drug administration, clean water can be used instead. For dispersal of study product in water, at least 5-10 ml of bottled, filtered or boiled water can be used in a clean container. Once placed in the liquid, the tablet should be allowed to completely disperse (after at least one minute) before providing the solution to the child to drink. Flavoring agent may be added to the liquid, if desired.

All children, caregivers and research staff will be blinded as to whether the child is in the amoxicillin DT or placebo DT treatment group until the end of the study once the decision to break the study blind is determined by the Sponsor (after completion of study primary manuscript). Codes linking randomization number for each child to actual treatment will be secured in a sealed, opaque envelope and maintained in a locked drawer in the research pharmacy.

Caregivers will be given the emergency contact number for the study personnel during the consenting process in order to report any adverse events.

## Stability and Storage

All study product not already dispensed to children will be stored in locked cabinets only accessible to the study pharmacists, study clinician, and investigators. The study product does not need to be refrigerated and will be stored in a dry location at ambient room temperatures below 25° C (77° F). Study product will be dispensed to participant caregivers as participant-specific kits by the study pharmacist and documented as such.

